**Figure 2 F2:**
[figure not shown]
Schedule of enrolment, intervention, and assessments. IgA, Immunoglobin A.

### Statistical analysis

The analysis of the data will be based on the intention-to-treat analysis and all recruited participants will be considered. Data normality will be examined using the Kolmogorov-Smirnov test. The variables will be reported as mean ± SD or median. The percentage changes for each variable will be calculated using the following formula in which *E* and *B* stand for the end value and the baseline value of the variable, respectively.

$$\left[\;\frac{E-B}{B\;\times \;100}\;\right]$$

In case of meeting the assumption of normality, the significant changes between the two groups will be evaluated using the independent t-test, otherwise, Mann-Whitney analysis will be used. Comparison of the mean of variables at baseline with that of post-intervention within each group will be conducted using paired *t*-test or Wilcoxon signed-rank test. In order to control any possible confounding variable, the analysis of covariance (ANCOVA) will be used when necessary.

All analyses will be performed using the Statistical Package for Social Sciences, version 22.0 (SPSS, Inc., Chicago, IL, United States) with statistical significance at *p *< 0.05.

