### Eligibility criteria

The inclusion criteria will be as followed: healthy, 6- to 12-year-old children, during the mixed dentition, no active or untreated carious lesions, no severe crowding, no marked inflammation in oral cavity.

The exclusion criteria will be the presence of any inflammatory disease and use of any medications, supplements, or probiotic intake within the last two weeks or during the intervention. The patients who fail to follow-up will also be excluded from the study.

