### Sample size

To calculate the sample size, we used the following comparing two means formula (α=0.05, significance; $\beta \;=\;0.1;{\bar{x}}_{1}\;=\;1.4,\;{\bar{x}}_{2}\;\;=\;\;-3.1,S_{1}\;\;=\;\;4.1,\;\text{and}\;S_{2}\;\;=\;\;5.9$) based on the available literature (23) with maximum 30% falls during the follow-up, the final sample size was 40 participants per arm, 80 in total.

n=(Z(1−β)+Z(1−α/α22))2(S12+S22)(x¯1−x¯2)2

The participants will be selected using the convenience non probability sampling method. So, from the beginning of the study, any patient who meets the inclusion criteria and does not have the exclusion criteria will be selected and this process will continue until the sample size is reached.

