### Adverse events

Since the study product will be in form of a toothpaste, minimal harm is expected. However, an adverse event (AE) has been defined as any unfavorable discomfort in the mouth during the study period. All the children and their parents will be advised to report any AE immediately and in case of AE, participant(s) will be excluded from the study.

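### The plan promises an intention-to-treat analysis of all recruited children, but three of its exclusion rules act after randomisation and, applied as written, leave a completer comparison under that label

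*Protocol article*

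**What the plan says.** The Protocol article, Statistical analysis, defines who is analysed: "The analysis of the data will be based on the intention-to-treat analysis and all recruited participants will be considered".

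Two other sections remove children from the study once it is under way:

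- Eligibility criteria, on loss to follow-up: "The patients who fail to follow-up will also be excluded from the study".
- Eligibility criteria, listing as an exclusion "use of any medications, supplements, or probiotic intake within the last two weeks or during the intervention". The second half of that window lies after allocation.
- Adverse events: "in case of AE, participant(s) will be excluded from the study". The threshold is low, since "an adverse event (AE) has been defined as any unfavorable discomfort in the mouth during the study period".

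The Sample size section allows for losses: "with maximum 30% falls during the follow-up, the final sample size was 40 participants per arm, 80 in total". The Outcomes section measures IgA and pH only at baseline and after four weeks. No section shown says that an excluded child stays under follow-up, gives the four-week sample, or remains in the analysis.

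**The concern.** Intention-to-treat protects the comparison because the children compared are those who were randomised, in the arms to which they were allocated. All three exclusion events happen after allocation, and each could depend on the paste received or on the state of the child's mouth. If the exclusions are carried out, the primary comparison is between children who finished, took no other product and had no mouth discomfort, while the report calls it intention-to-treat.

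The article itself suggests how exclusions might differ by arm. The pastes differ only in the postbiotic ingredient, so any effect of that ingredient on mouth discomfort would produce adverse-event exclusions in one arm and not the other. The Discussion cites postbiotics as reducing respiratory infection in children. If that held here, fewer children on the active paste might need medication and so be excluded. Children who need medication or have oral discomfort may plausibly differ in salivary IgA or pH. The adverse-event rule is the most exposed of the three because of its low threshold.

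**Working it through.** **Step 1. The plan's own sample size.** Inputs from Sample size: two-sided alpha 0.05 (the formula uses Z at 1 − α/2), β = 0.1, means 1.4 and −3.1 (difference 4.5), SDs 4.1 and 5.9.

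- n = (1.282 + 1.960)² × (4.1² + 5.9²) / 4.5² = 26.78, so 27 per arm.
- Allowing for 30% loss: 27 / 0.70 = 38.6, so 39 per arm. With the t-distribution, 28 per arm are needed, and 28 / 0.70 = 40.

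The stated 40 per arm is reproduced. The allowance treats lost children as absent from the analysis: up to 0.30 × 40 = 12 per arm, or 24 of 80.

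**Step 2. Can the rules be applied together?** A child who reports mouth discomfort in week 2 is, under Adverse events, excluded from the study. Under Statistical analysis the same child is to be considered. The percentage change and the paired tests both need an end value, and the only end value is at four weeks. If exclusion means that the child leaves follow-up, no such value is taken. The same holds for a child excluded for medication use.

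**Step 3. Power.** At the planning inputs, 40 per arm give 97.7% power (normal approximation) or 97.5% (t), and 28 per arm give 91.2% or 90.2%. Losing 30% leaves power at the planned 90%, so what matters is which children are compared.

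**Step 4. Possible bias.** Let p1 and p0 be the proportions excluded in the two arms, and let δ be the mean gap between excluded and retained children, taken as equal in both arms. The retained mean in an arm differs from the mean of all its randomised children by p × δ, so the comparison is off by (p1 − p0) × δ. The planning SD is √((4.1² + 5.9²)/2) = 5.08. The documents give no value for p1, p0 or δ, so the following are assumptions:

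- Equal proportions: 0 × δ = 0.
- 30% versus 10%, gap 0.5 SD: 0.20 × 0.5 × 5.08 = 0.51 units, 11% of 4.5.
- 30% versus 10%, gap 1 SD: 0.20 × 1.0 × 5.08 = 1.02 units, 23% of 4.5.

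**Step 5. Effect on the test.** Assume no true effect, exclusions in one arm only, and 40 per arm at the start:

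- 10% excluded, gap 0.25 SD: shift 0.13 units, two-sided type I error about 5.1%.
- 20% excluded, gap 0.5 SD: shift 0.51 units, about 7.1%.
- 20% excluded, gap 1 SD: shift 1.02 units, about 13.5%.

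**The case against.** Several stronger readings are tempting, and the documents do not support them.

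- A reader might infer that the promised analysis set cannot exist. That goes too far. Exclusion from the study could have been meant as withdrawal from the product and visits, with the child still analysed as randomised. The flow diagram, which might show the analysis set, is not available. What stands is that the text does not say so and the sections conflict as written.
- A reader might object that no missing-data method is given. A journal article commonly leaves this to a full protocol or analysis plan, so it is not a fault here. Such a plan could add a method, but it could not make both the exclusion rules and the intention-to-treat statement true, nor recover samples never taken.
- A reader might infer that bias is certain or large. The 30% in the Sample size section is a maximum allowance for losses and says nothing about imbalance. Placing all of it in one arm with a 1 SD gap gives 0.30 × 5.08 = 1.52 units (34% of 4.5), but that is a corner case. The pastes match in packaging, color, taste and scent, participants and the outcome assessor are blinded, and minimal harm is expected, all of which argue against large differences between arms.
- A reader might infer that the adverse-event rule discards the safety information. Adverse events are to be reported immediately, so the event is known before exclusion, and nothing says that it goes uncounted.
- A reader might expect imputation to settle the matter. With only baseline and week 4 measured, imputing from arm and baseline gives essentially the complete-case covariance-adjusted answer and would not remove bias that depends on the outcome itself.

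These points limit the claim about size and consequence. They do not remove the contradiction over who is in the primary comparison.

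**Conclusion.** The point holds as an internal contradiction about the primary analysis set, and the plan is wrong as written. If the exclusion rules are followed, the result is a completer or complier comparison carrying an intention-to-treat label, and it is open to bias if exclusions differ by arm and relate to IgA or pH.

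The size cannot be derived from the documents. It starts at zero, for exclusions balanced and similar in both arms, where only precision is lost and the sample size already covers that. The illustrative range of about 0.5 to 1.0 units rests wholly on the assumed 30% versus 10% exclusion, an assumed gap of 0.5 to 1 SD equal in both arms, and the planning SD of 5.08. The matter should be settled before follow-up is complete, because a four-week sample not taken cannot be recovered.

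**What to change.** Reconcile Eligibility criteria, Adverse events and Statistical analysis so that they describe one analysis set:

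- Limit the exclusion criteria to the child's status before randomisation.
- Separate stopping the product from leaving follow-up and leaving the analysis. Whether a child stops the product after an adverse event or medication use is a clinical decision and is not judged here.
- Seek the week-4 saliva sample from every randomised child where possible. It will not be obtainable from children truly lost.
- As the primary analysis, compare all randomised children with data in their allocated arms. Add a sensitivity analysis for children whose week-4 value is truly missing, showing how far the result moves if they differ from those observed. Imputation is optional.
- Label any set without the excluded children per-protocol.
- Report adverse events by randomised arm.

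The cost is a wording change in three sections, a few extra week-4 samples and a small amount of analysis. No additional children are needed.

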**Methods:**

The aim of this triple-blind, randomized, placebo-controlled trial is to investigate the effect of postbiotic-toothpaste (*Bifidobacterium animalis subsp. animalis*) on salivary levels of Immunoglobulin A (IgA) and pH in children. Using comparing two means formula to calculate the sample size, for this trial 80 healthy 6- to 12-year-old children during mixed dentition with no cavitated dental caries will be selected by convenience sampling method and randomly allocated to two groups, postbiotic-toothpaste or placebo-toothpaste. Saliva samples will be gathered at baseline and four weeks after the intervention. The level of salivary IgA will be determined by ELISA and salivary pH will be measured using a pH meter. Data will be compared within and between groups using independent t-test and paired t-test, in case of normality, with a *p *< 0.05 as statistically significant.

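### A normality pre-test picks the primary comparison, so the IgA effect measure is not fixed in advance; pre-specify one baseline-adjusted ANCOVA instead

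*Protocol article*

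**What the plan says.** In the protocol article, Statistical analysis, the rule has two steps. First, "Data normality will be examined using the Kolmogorov-Smirnov test". Then changes between the groups are compared with the independent t-test if normality is met; "otherwise, Mann-Whitney analysis will be used". The Abstract (Methods) carries the same condition: t-tests are used "in case of normality". The summary statistic is likewise left open between mean with SD and median. ANCOVA appears only as an option for controlling confounders where the need arises. It is not tied to the primary comparison, and baseline IgA is not named as a covariate.

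Under Outcomes, the primary outcome is salivary IgA in mg/100ml, measured at baseline and after four weeks. Under Sample size, the trial is sized on a difference between two means (1.4 and -3.1, SDs 4.1 and 5.9, β = 0.1), and "with maximum 30% falls during the follow-up, the final sample size was 40 participants per arm, 80 in total".

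**The concern.** A t-test and a Mann-Whitney test answer different questions: one concerns a difference in means, the other a rank ordering. If the observed distribution picks between them, the quantity that the trial estimates is known only after the data are seen. Only one of the two possible quantities matches the sample size calculation.

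Two things are at stake. One is clarity about the primary result, since near the 5% boundary the two tests can disagree. The other is precision: whichever test is chosen, the default is a comparison of changes without a baseline covariate, although baseline IgA is measured in every child.

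The statement in the article is itself a fixed rule, so this is not a matter of detail left to an unseen analysis plan.

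**Working it through.** **1. The plan's own figure.** Inputs from Sample size: α = 0.05 two-sided, β = 0.1, means 1.4 and -3.1 (difference 4.5), SDs 4.1 and 5.9.

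n = (1.960 + 1.282)² × (4.1² + 5.9²) / 4.5² = 10.51 × 51.62 / 20.25 = 26.8, so 27 per arm. With 30% loss, 27 / 0.7 = 38.6, so 39. The plan states 40, which is reproduced within rounding. Complete cases at maximum loss: 40 × 0.7 = 28 per arm. The checks below therefore use 28 and 40.

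A mean of -3.1 cannot be a concentration, so the inputs look like changes (an inference).

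**2. What the pre-test detects.** The article gives no distribution for IgA, so log-normal data are assumed. The test uses the mean and SD estimated from the same sample. Share of simulated samples flagged as non-normal (10,000 per setting):

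| log-SD (CV) | n=28, uncorrected | n=28, Lilliefors | n=40, uncorrected | n=40, Lilliefors |
|---|---|---|---|---|
| 0.3 (31%) | 0.4% | 20% | 0.7% | 27% |
| 0.5 (53%) | 3% | 46% | 7% | 61% |
| 0.6 (66%) | 7% | 59% | 15% | 75% |
| 0.8 (95%) | 19% | 80% | 39% | 92% |
| 1.0 (131%) | 38% | 92% | 64% | 98% |

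For CV 50-70% this is about 3-18% uncorrected and 43-79% with Lilliefors. On truly normal data the uncorrected test rejects about 0.01% of samples instead of 5%. Which primary test is run thus depends heavily on the version of the pre-test.

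**3. What the two-stage rule costs.** Assumptions: log-normal IgA, baseline correlation r = 0.5, 28 per arm, pre-test applied to changes in each arm, true ratios 1.35, 1.42 and 1.49 for CV 40%, 50% and 60%. Power from 6,000 simulated trials per setting:

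| Analysis | CV 40% | CV 50% | CV 60% |
|---|---|---|---|
| t-test on change | 82.5% | 77.0% | 72.8% |
| Mann-Whitney on change | 82.3% | 77.6% | 74.3% |
| Two-stage, uncorrected | 82.5% | 77.2% | 73.2% |
| Two-stage, Lilliefors | 83.0% | 77.6% | 74.5% |
| t-test on log change | 81.7% | 78.0% | 75.3% |
| ANCOVA, raw scale | 87.4% | 82.2% | 78.5% |
| ANCOVA, log scale | 89.9% | 87.8% | 85.4% |

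- The two-stage rows lie within about 2 points of either fixed test. Type I error of the rule was 4.7-5.0% here, and 4.8-5.7% when end values were tested instead.
- Raw ANCOVA minus the uncorrected two-stage rule: 87.4 - 82.5 = 4.9, 82.2 - 77.2 = 5.0, 78.5 - 73.2 = 5.3 points.
- Log ANCOVA minus raw ANCOVA: 2.5, 5.6 and 6.9 points; about 3-8 over repeated runs.
- The log scale without the covariate moves power by only -1 to +2 points against the two-stage rule.

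**4. Why the covariate matters.** With equal variances, a change score has variance 2σ²(1 - r) and ANCOVA has σ²(1 - r²). The ratio is (1 + r)/2 = 0.75 at r = 0.5. For normal data, simulation gives 92-93% for raw ANCOVA against 84-86% for the change-score comparison.

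Applied to the plan's inputs, read as changes: pooled SD = √(51.62/2) = 5.08. At 28 per arm, 4.5 / (5.08 × √(2/28)) = 3.31, and 3.31 - 1.96 = 1.35, or 91% power. With ANCOVA, 3.31 / √0.75 = 3.83, and 3.83 - 1.96 = 1.87, or 97%.

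**The case against.** The strongest reply is that the pre-test does no measurable harm. That stands as far as error rates go: power and type I error under the two-stage rule match those of a fixed test. What remains is that the estimated quantity is not settled. In the log-normal setting of step 3, the t-test and Mann-Whitney disagreed on significance in 7-11% of simulated trials.

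A reader might also infer four stronger points, which the document does not support:

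- *The Kolmogorov-Smirnov test almost never finds skewness at this size.* This holds only for the uncorrected version with mild to moderate skew. The article does not say which version applies, and with Lilliefors detection is moderate to high.
- *Baseline adjustment is ruled out once a rank test is chosen.* The article attaches no normality condition to ANCOVA, and a rank test on changes already uses baseline.
- *IgA is skewed, so a log scale is required.* The article says nothing about its distribution. Log-scale ANCOVA wins in the simulation partly because the data were generated to suit it. If IgA is normal it loses about 1-2 points.
- *The article is at fault for not saying which variable, or which arm, is tested for normality.* That detail may stand in an analysis plan that is not shown, and it is not counted here.

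It is also fair to say that fixing one raw-scale test would cure the main complaint. It would, but it would leave the baseline information unused.

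**Conclusion.** The point holds in a limited form. The plan lets a pre-test of low to moderate, version-dependent power choose between a mean and a rank comparison for the primary outcome, while the sample size assumes a mean difference. The consequence is an effect measure not fixed in advance, not an inflated error rate.

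The loss that can be recovered comes from the unadjusted comparison of changes: about 5 points of power if IgA is log-normal and up to about 8 if it is normal, with r = 0.5 and 28 per arm. A pre-set log scale would add about 3-8 points only if IgA is log-normal. The CVs, the correlation, the effect ratios and log-normality are all assumptions. The case for one pre-set effect measure does not depend on any of them.

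**What to change.** In Statistical analysis, and correspondingly in the Abstract:

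- Delete the normality rule as the selector of the between-group test.
- State one primary analysis: four-week IgA compared between arms by ANCOVA with baseline IgA as covariate, reported with the estimate, 95% CI and p-value.
- Fix the scale before unblinding. Raw IgA keeps the result in mg/100ml and the link to the sample size. Log IgA with log baseline, reported as a geometric-mean ratio beside arithmetic means in mg/100ml, is a reasonable alternative.
- Analyse pH, already a log measure, untransformed with its own baseline as covariate.
- Name one rank-based sensitivity analysis and report it whatever the distribution looks like. Inspect residuals by plot, without letting the plot change the primary analysis.

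The cost is wording only: no further children, samples or visits. If the log scale is chosen, the effect is a ratio and no longer matches the mean-difference basis of the sample size. The protocol gives no log-scale SD or target ratio from which to restate it, so this should be acknowledged or new inputs supplied.

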### Outcomes

The primary outcome of this study will be the salivary IgA levels of the children and will be reported in mg/100ml. The secondary outcome will be the pH levels of saliva in children. The primary and secondary outcomes will be assessed at the baseline, before any intervention, and after four weeks of intervention.

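### The percentage-change formula has its 100 in the denominator and is applied to pH as well as IgA, and the between-group test is on an unadjusted change whose scale is not fixed

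*Protocol article*

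**What the plan says.** The Outcomes section gives the primary outcome as "salivary IgA levels of the children and will be reported in mg/100ml", and adds: "The secondary outcome will be the pH levels of saliva in children". Both are measured at baseline and after four weeks.

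The Statistical analysis section states: "The percentage changes for each variable will be calculated using the following formula in which" E and B are the end and baseline values. The displayed fraction has E − B above the line and B × 100 below it. The next paragraph says that, if normality holds, "the significant changes between the two groups will be evaluated using the independent t-test", with Mann-Whitney otherwise. Within-group comparisons use paired tests. ANCOVA is to be used only where it is found necessary to control confounding.

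The Sample size section says: "To calculate the sample size, we used the following comparing two means formula". Its inputs are means 1.4 and −3.1, SDs 4.1 and 5.9, α = 0.05 and β = 0.1. No unit is attached to the means or SDs, and the section does not say whether they are absolute or percentage changes.

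**The concern.** Three things are fixed badly in one short section.

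- **The formula is not a percentage.** It is the only derived variable the analysis section defines. If it is programmed as printed, every summary of percentage change is wrong in size.
- **It covers pH.** pH is the logarithm of a concentration and its zero has no special meaning, so dividing a pH difference by the baseline pH gives a number that cannot be interpreted.
- **The tested quantity is left open.** The between-group test is on changes, but the text does not say which kind. Absolute and percentage change can give different p-values on the same data, so the primary result could depend on a choice made after the data are seen. Either choice is an unadjusted change score, although a baseline IgA is collected from every child and adjusting for it would normally give a more precise comparison.

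**Working it through.** **1. Does the formula touch the sample size?** The inputs are those of the Sample size section.

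n = (z₀.₉₀ + z₀.₉₇₅)² × (S₁² + S₂²)/(x̄₁ − x̄₂)²

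- (1.2816 + 1.9600)² = 10.507
- 4.1² + 5.9² = 16.81 + 34.81 = 51.62
- (1.4 − (−3.1))² = 4.5² = 20.25
- n = 10.507 × 51.62/20.25 = 26.8, so 27 per arm
- 30% loss: 27/0.7 = 38.6, so 39 per arm
- t-distribution version: 27.8, so 28 per arm, and 28/0.7 = 40

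The stated 40 per arm is reproduced. The percentage formula plays no part in it.

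**2. Size of the formula error.** Correct: 100 × (E − B)/B. Printed: (E − B)/(100 × B). Their ratio is 100 × 100 = 10,000 for any E and B. The values below are illustrative and not from the protocol.

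| | B | E | Printed | Correct |
|---|---|---|---|---|
| IgA, mg/100 ml | 10 | 12 | 0.002 | 20% |
| pH | 7.0 | 7.2 | 0.000286 | 2.86% |

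**3. Effect on tests.** Dividing every value by the same constant leaves t and rank statistics unchanged. On one simulated data set (40 per arm) the printed and correct versions both gave t = 3.174, t-test p = 0.00215 and Mann-Whitney p = 0.00052. Absolute change on the same data gave t-test p = 0.00256. So the misplaced 100 cannot alter a p-value, but the unfixed scale can.

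**4. pH.** A rise of 0.2 units multiplies hydrogen-ion concentration by 10^(−0.2) = 0.631, a fall of about 37%, wherever it starts. As a percentage of pH, the same shift is 0.2/7.0 = 2.86% from 7.0 and 0.2/6.5 = 3.08% from 6.5. Identical chemical changes receive different percentages.

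**5. Cost of an unadjusted change score.** The protocol gives no CV, baseline to follow-up correlation or effect ratio for IgA, so all three are assumed here. The simulation uses log-normal IgA, 40 × 0.7 = 28 completers per arm, two-sided 5% tests and 40,000 replicates per row. The Monte Carlo standard error is about 0.002.

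| CV | r | True ratio | t-test, % change | t-test, absolute change | Log ANCOVA | Gain over absolute | Gain over % |
|---|---|---|---|---|---|---|---|
| 0.4 | 0.5 | 1.35 | 0.790 | 0.823 | 0.905 | 8.2 | 11.5 |
| 0.5 | 0.5 | 1.42 | 0.737 | 0.774 | 0.876 | 10.2 | 13.9 |
| 0.6 | 0.5 | 1.49 | 0.693 | 0.726 | 0.856 | 13.0 | 16.3 |
| 0.5 | 0.6 | 1.42 | 0.831 | 0.848 | 0.920 | 7.2 | 8.9 |
| 0.5 | 0.7 | 1.35 | 0.832 | 0.831 | 0.898 | 6.7 | 6.6 |

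A shorter run on the same inputs gave gains of about 6–13 points over absolute change and 8–16 over percentage change, which agrees within simulation error. Percentage against absolute change differs by −3.7 to +0.1 points. Most of the gain therefore comes from replacing an unadjusted raw-scale change score, and little from avoiding the percentage scale.

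**The case against.** The strongest reply is that the formula is a slip, perhaps of typesetting. The text calls the result a percentage change, so the intent is clear, and a 20% rise printed as 0.002 would be noticed. This stands as far as likely harm goes: a reader might infer that every percentage in the trial report will be wrong, but that follows only if the formula is used literally. The printed rule is still wrong.

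A reader might also infer that percentage change is what the t-test compares, since it is the only change defined beforehand. The text does not say so, and an outcome in mg/100 ml fits absolute change at least as well. The power figures for percentage change therefore describe one possible reading and are not a property of the plan.

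A third tempting inference is that percentage change is the wrong scale for the stated sample size. The negative mean shows that 1.4 and −3.1 are changes and not concentrations. Nothing shows whether they are absolute or percentage changes, so no mismatch can be demonstrated.

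It is also fair to say that ANCOVA is already mentioned, that a separate analysis plan may settle its use, and that the planned switch to Mann-Whitney would recover some power. With that switch applied to percentage change (normality tested within each arm at 5%, an assumption), power in the five scenarios was 0.805, 0.763, 0.743, 0.847 and 0.839. That is still below log ANCOVA in each. For pH, levels are reported as well and no percentage test is stated, so that part concerns presentation.

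**Conclusion.** The point holds within limits. The printed formula is wrong by a factor of exactly 10,000, which affects reported magnitudes but no p-value and not the sample size. Its application to pH yields a summary that cannot be interpreted. The between-group comparison is on unadjusted changes of unspecified scale.

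The first two parts follow from the text and algebra alone. The power gain from baseline-adjusted log IgA, about 7–13 points over absolute change and 7–16 over percentage change, rests on assumed log-normality, CV 40–60%, r 0.5–0.7, ratios 1.35–1.49 and 28 completers per arm. It should not be charged to the misplaced 100. On the sample size, all that can be said is that the scale and unit of 1.4 and −3.1 are not stated.

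**What to change.** 1. Print the formula as 100 × (E − B)/B, restrict it to IgA and label it descriptive.
2. Report pH as the absolute difference in pH units.
3. Name the primary between-group comparison: week-4 IgA adjusted for baseline IgA by ANCOVA, on the log scale if IgA is skewed. If the log scale is used, give the back-transformed ratio between arms with its confidence interval; that ratio also supplies a percentage effect.
4. State the scale and unit of 1.4 and −3.1 in the Sample size section.

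This costs one corrected formula and a few sentences. The baseline sample is already planned, so no extra data or children are needed. The analysis choice should be recorded before unblinding.

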### Study product and intervention

The postbiotic strain *Bifidobacterium animalis subsp. animalis* PTCC1631 will be used. The intervention will be in form of a postbiotic-toothpaste (*B. animalis subsp. animalis, 10*^*9*^^*CFU*^/*g* (22)). The postbiotic strain was ordered from the Persian Type Culture Collection center, a subset of the Iranian Research Organization for Science and Technology. The postbiotic and placebo-toothpaste are similar in packaging, color, taste, and scent, and the only difference is the absence of the postbiotic ingredient in the placebo-toothpaste. Table 1 shows the ingredients of the toothpastes.

**Table 1 T1:** List of the ingredients of each toothpaste.

	Postbiotic-toothpaste (100 gr)	Placebo-toothpaste (100 gr)
*B. animalis subsp. animalis*	1–5 gr	
Sorbitol	30–40 gr	30–40 gr
Glycerin	20–30 gr	20–30 gr
Calcium carbonate	15–25	15–25
Carboxy methyl cellulose	1–2 gr	1–2 gr
Sodium saccharin	0.1–0.5 gr	0.1–0.5 gr
Sodium lauryl ether sulfate	2–5 gr	2–5 gr
Strawberry flavor	1–2 gr	1–2 gr
Distilled water	qs to 21 ml	qs to 21 ml

Eligible participants will be randomly allocated to two groups, intervention and control. The postbiotic-toothpaste will be given to the children in the intervention group and the children in the control group will receive the placebo-toothpaste. Children in both groups will be asked to brush their teeth twice a day (in the morning and at night) for two minutes, under the supervision of their parents, for four weeks. To eliminate any possible confounding effect of the method of tooth-brushing on the results, children and their parents will be instructed on how, when, and how long to brush their teeth at the beginning of the study.

In order to ensure participants adherence, parents will receive a message on a weekly basis to remind them the importance of tooth-brushing twice a day. Also, to motivate and encourage the children, they will be asked to record daily short videos of themselves while brushing their teeth and put it all together at the end of the four weeks.

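### Paired tests within each arm are planned as significance tests beside the between-arm test, but a within-arm p-value cannot separate the postbiotic from changes that both arms share

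*Protocol article*

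**What the plan says.** All of the following is in the protocol article.

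- **Statistical analysis, between arms.** Changes in the two groups are compared with an independent t-test, or a Mann-Whitney test if normality fails. ANCOVA is named as well, to be used if needed to control confounders.
- **Statistical analysis, within arms.** "Comparison of the mean of variables at baseline with that of post-intervention within each group will be conducted using paired" t-test or Wilcoxon signed-rank test. The section closes by placing all analyses under one rule, "with statistical significance at" p<0.05.
- **Abstract, Methods.** The two comparisons appear side by side: "Data will be compared within and between groups using independent t-test and paired t-test, in case of normality".
- **Objectives.** The hypothesis is that daily use of the postbiotic paste can raise salivary IgA. Placebo is not mentioned in it.
- **Study product and intervention.** In both groups "children and their parents will be instructed on how, when, and how long to brush their teeth at the beginning of the study". Both groups also brush twice a day under parental supervision, receive weekly reminder messages and make daily videos. Table 1 gives the two pastes the same base.
- **Sample size.** The calculation rests on a comparison of two means, and "the final sample size was 40 participants per arm, 80 in total".

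**The concern.** A paired test in the postbiotic arm asks whether IgA changed over four weeks. It does not ask whether IgA changed more than it would have with placebo. Taught and supervised brushing, reminders and the common paste base could each move saliva measurements in both arms. Such a shared change cancels in the between-arm comparison and stays in full in a within-arm one.

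The hypothesis, read literally, could be met by a before/after rise alone. A report of a significant rise with the postbiotic paste and a non-significant one with placebo would then look like a positive trial. That pattern is not evidence that the arms differ. At stake is a conclusion of efficacy for a paste whose active ingredient has done nothing.

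**Working it through.** **1. Which test the plan is sized on.** Inputs from Sample size: "α=0.05, significance"; β=0.1; means 1.4 and −3.1 (difference 4.5); SDs 4.1 and 5.9; "with maximum 30% falls during the follow-up". The printed critical value is garbled in extraction and is read here as two-sided, Z(1−α/2).

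- n = (1.2816 + 1.9600)² × (4.1² + 5.9²) / 4.5² = 10.507 × 51.62 / 20.25 = 26.78, so 27 per arm.
- 27 / 0.70 = 38.6, so 39 per arm after loss, against 40 stated. A one-sided reading gives 22, then 32, and does not match.

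The stated size is therefore reproduced to within one child per arm as a two-sided between-arm comparison. The paired tests play no part in it.

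**2. Chance of significance in the postbiotic arm only, with no postbiotic effect.** Assume both arms shift by the same amount and let p be the power of each paired test. The arms are independent, so the probability is p × (1−p):

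- p = 0.5: 0.5 × 0.5 = 25%, the maximum of this expression.
- p = 0.2 or 0.8: 0.2 × 0.8 = 16%.
- No shift, counting only a rise: 0.025 × 0.95 = 2.4%. Counting either direction: 0.05 × 0.95 = 4.75%.

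**3. What shifts would produce such values of p.** The documents give no expected common shift, so a range is shown. Assumption: 4.1 and 5.9 are SDs of within-child change. One negative mean suggests this, but the article does not say it. Their root mean square is √(51.62/2) = 5.08. The power of the paired t-test comes from the noncentral t distribution with n−1 degrees of freedom and noncentrality (shift/SD) × √n. For example, 1.5/5.08 × √40 = 1.87, which gives p = 0.445, and 0.445 × 0.555 = 0.247.

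| Common rise (SD 5.08, n=40 per arm) | Significant rise in postbiotic arm | Significant in postbiotic arm only |
|---|---|---|
| 0 | 2.5% | 2.4% |
| 1.0 | 23% | 18% |
| 1.5 | 44% | 25% |
| 2.0 | 68% | 22% |
| 3.1 | 96% | 3% |

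Across SDs from 5.9 down to 4.1, the middle column runs over 18–32% at a rise of 1.0, 35–62% at 1.5 and 55–85% at 2.0. With 28 per arm (40 × 0.70) and SD 5.08, the last column is 14%, 22% and 25% at rises of 1.0, 1.5 and 2.0.

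**4. The between-arm test in the same settings.** In 40,000 simulated trials per setting, with shifts of 0 to 3.1 and 40 or 28 per arm, it was significant in 4.8–5.1%. That is the nominal 5% two-sided, or 2.5% in favour of the postbiotic, whatever the common shift.

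**The case against.** The strongest reply is that the plan already contains the right comparison. The between-arm test is listed first, the sample size is built on it, and the design is randomised and placebo-controlled. A closing sentence that gives one alpha for all analyses does not rank the tests, and which test is confirmatory is often settled in an analysis plan, which is not shown. The Discussion is mixed evidence of intent: it cites before/after rises from earlier studies, but it also reports a placebo comparison as not significant. All of this stands.

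Three stronger readings therefore fail:

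- A reader might infer that the trial will claim efficacy from a paired test. No sentence says so. The middle column of the table would be a false-claim rate only under a decision rule that the article does not contain.
- A reader might infer that randomisation is thrown away. It is not, because the randomised comparison is kept and powered.
- A reader might add regression to the mean as a cause of within-arm change. Nothing in Eligibility criteria selects children on IgA or pH, so the documents give no basis for a systematic effect of that kind.

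The 25% is also a worst case. It needs an unknown shift that puts each paired test at 50% power, and the pattern is rare with no shift and fades again with a large one.

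What the reply does not remove is that the article itself states the within-arm significance tests, in two places. This is a stated analysis that cannot answer the trial's question, not a detail left for later.

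**Conclusion.** The point holds as one about the role of the within-arm tests. They are planned at p<0.05 next to the between-arm test, under a hypothesis that does not mention placebo, and they cannot distinguish the postbiotic from influences common to both arms. If they were used to judge efficacy, an inert postbiotic could appear significant in its own arm only in up to 25% of trials, against 2.5% in its favour for the between-arm test.

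The p(1−p) result rests on independent arms and an equal shift in both. The table rests further on assumed shifts and on reading the planning SDs as SDs of change. The shared brushing programme makes a common shift plausible, but the documents do not give its size. The change should be made; it does not call the design or the sample size into question.

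**What to change.** In the Abstract (Methods) and in Statistical analysis, state that efficacy is judged only on the between-arm difference in week-4 salivary IgA, adjusted for baseline IgA by ANCOVA. The article already names ANCOVA, and baseline IgA is already collected. Present within-arm changes descriptively, as mean change with 95% confidence interval, and not as tests of efficacy. The hypothesis in Objectives can be worded in the same edit as a difference from placebo.

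The cost is wording only. Sample size, visits and data collection stay as they are, and fewer tests are run.
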